## Abstract

**Background:**

The overuse of antimicrobials is recognized as the main selective pressure driving the emergence and spread of antimicrobial resistance in human bacterial pathogens. Urinary tract infections (UTIs) are among the most common infections presented in primary care and empirical antimicrobial treatment is currently recommended. Previous research has identified that a substantial proportion of Irish general practitioners (GPs) prescribe antimicrobials for UTIs that are not in accordance with the Guidelines for Antimicrobial Prescribing in Primary Care in Ireland. The aim of this trial is to design, implement and evaluate the effectiveness of a complex intervention on GP antimicrobial prescribing and adult (18 years of age and over) patients’ antimicrobial consumption when presenting with a suspected UTI.

**Methods/design:**

The Supporting the Improvement and Management of Prescribing for urinary tract infections (SIMPle) study is a three-armed intervention with practice-level randomization. Adult patients presenting with suspected UTIs in primary care will be included in the study.

The intervention integrates components for both GPs and patients. For GPs the intervention includes interactive workshops, audit and feedback reports and automated electronic prompts summarizing recommended first-line antimicrobial treatment and, for one intervention arm, a recommendation to consider delayed antimicrobial treatment. For patients, multimedia applications and information leaflets are included. Thirty practices will be recruited to the study; laboratory data indicate that 2,038 patients will be prescribed an antimicrobial in the study. The primary outcome is a change in prescribing of first-line antimicrobials for UTIs in accordance with the Guidelines for Antimicrobial Prescribing in Primary Care in Ireland. The study will take place over 15 months with a six-month intervention period. Data will be collected through a remote electronic anonymized data-extraction system, a text-messaging system and GP and patient interviews and surveys. The intervention will be strengthened by the implementation of a social marketing framework and an economic evaluation.

**Trial registration:**

This intervention is registered at ClinicalTrials.gov, ID
NCT01913860.

## Background

Antimicrobial resistance (AMR) is an important and complex public health problem
[1]. The spread of AMR has led to the increased use of reserved antimicrobial agents
[2] in an era where few new antimicrobial agents are in production
[3].

Today, 80% of antimicrobial prescribing takes place in the community by general practitioners (GPs)
[4]. Ireland is one of only three countries in Europe where the level of outpatient antimicrobial prescribing is increasing
[5,6]. Within this context, the inappropriate and over-prescription of antimicrobials by GPs is a recognized factor contributing to the spread of AMR
[7-10]. The Guidelines for Antimicrobial Prescribing in Primary Care in Ireland
[11] provide advice on the selection of antimicrobial drugs for common infections and recommend the use of specific antimicrobials, with reserved drugs for more serious infections. However, despite the widespread availability of these guidelines, recent research has identified that less than 40% of outpatient prescriptions for urinary tract infections (UTIs) are made out according to first-line recommendations
[12].

Urinary tract infections are predominantly caused by a bacteria; *Escherichia coli*[6,13,14], and are generally treated empirically, prior to the results of antimicrobial susceptibility testing
[11,12,15]. Antimicrobial resistance is now a critical factor in the treatment of UTIs
[9,12,16], the second most common bacterial infection in primary care
[6,12,13,15,17].

### Changing prescribing and consumption antimicrobial behaviours

Antimicrobial resistance is complex
[7,18], dynamic
[19] and continuous
[20], meaning that no single solution will manage the problem effectively. Multifaceted interventions aimed at multiple stakeholders (GP, patients and the wider community) have been shown to be successful in reducing inappropriate prescribing
[2,21-23] and can bring about social change by addressing local barriers to change
[24]. Patients may have preconceived expectations of the consultation
[23], determined by their prior experience within the practice and the treatment of a recurring condition in some cases
[25]. However, a review of patient-orientated interventions to improve antimicrobial prescribing concluded that change is better achieved by encouraging health professionals rather than by educating patients about the negative aspects of antimicrobials
[2]. The GP’s decision to prescribe antimicrobials should be a balance between the treatment of the individual in the short term and its harmful impact on society in the long term
[19,26]. General practitioners prescribe antimicrobials to treat (bacterial) infection, to guard against the risk of a missed diagnosis
[19], or because they believe the patient expects this outcome from the consultation
[25]; therefore, to obtain a behavioural change, many factors need to be addressed
[27].

Educational interventions aimed at the prescriber, the GP, have shown some successes. Improvements in overall prescribing practices in primary care have been linked with the use of small interactive workshops with health care professionals, which provide a greater change in prescribing behaviours when compared with a passive lecture-style format
[28-31]. An interactive workshop style is more likely to identify multifactorial causes in inappropriate prescribing, leading to the provision of tailored behavioural change methods for GPs
[2]. Electronic prescribing prompts have successfully increased GP adherence to prescribing guidelines for a range of common illnesses
[32-34]. Electronic prompts have also been successful in increasing the use of specific antimicrobial drug choices, such as first-line antimicrobial treatment for common infections
[35]. Currently, prescribing prompts are not commonly available within GP patient management software systems in Ireland.

The use of audit and feedback of information in conjunction with other intervention methods (delayed prescribing, educational material or electronic prompts) has also proven effective in improving GPs antimicrobial prescribing behaviours
[2,36]. General practitioners in the UK receive routine feedback on their prescribing practices and are among the lowest community prescribers of antimicrobials in Europe
[30,37]. Currently, Irish GPs cannot readily access information on their prescribing practices, despite evidence to suggest that feedback can successfully reduce antimicrobial prescribing in the Irish primary care setting
[36].

The use of delayed antimicrobial prescribing for viral infections in primary care in the UK has been credited with achieving a 50% reduction in antimicrobial use
[22,38,39]. Empirical antimicrobial treatment for UTIs is currently recommended in the Guidelines for Antimicrobial Prescribing in Primary Care in Ireland
[11]. However, in at least 50% of patients with UTIs, an antimicrobial may not be required, as the infection resolves naturally
[40-42]. Qualitative studies investigating attitudes to delayed antimicrobial prescribing in primary care have indicated that both patients and GPs are satisfied with this treatment format and welcome this 'safety net’ approach as a feasible treatment strategy
[23,43-45].

Between the GP and patient, the communication of such treatment strategies as delayed prescribing can be viewed as part of a shared decision-making process
[23]. A shared decision-making process can empower patients through a greater understanding of the issues involved
[46,47]. Shared decision making with delayed prescribing allows patients to prioritize what they value most; increasing their chances of a quick recovery or reducing their chances of side effects and reconsultations in the future
[47,48].

The leading systematic review in the area of complex prescribing interventions in primary care called for innovative intervention methods to be developed
[2]. Around 75% of a general practice’s registered patients will wait in the practice waiting room each year and the demand for easy-to-understand healthcare information is increasing
[49]. The use of informative material in GPs waiting rooms, such as educational videos and interactive games, to create awareness and explain the problems associated with the overuse of antimicrobials in primary care, has also been recommended through the European Antibiotics Awareness Day
[50].

Educational videos displayed in the practice waiting room can also increase patients’ understanding and satisfaction of their care, as well as empowering patients to discuss their treatments further with the GP
[51,52]. Previous research examined the effectiveness of a multimedia campaign in comparison with a static educational brochure to improve treatment for chronic illness in practice waiting rooms with patients with low health literacy
[53,54]. This approach was considered novel, effective and acceptable in improving health care management, by empowering patients to discuss making positive changes to their treatment with their GP
[54]. Audiovisual messages played in practice waiting rooms have also proven effective in increasing patient uptake of vaccines
[55].

Mobile phone technology can facilitate rapid and cost-effective access to a study group of interest to facilitate data collection. Previous programmes have successfully used text messages to assess consumption and adherence to antimicrobial treatments with 72% patient participation for follow-up
[56].

### Intervention development overview

Social marketing is the conceptual framework that guided the development of this intervention, by integrating knowledge from such disciplines as psychology, anthropology and sociology
[57-59] with commercial marketing techniques
[59-63]. Social marketing interventions address three key areas: understanding current behaviours; identifying determinants and identifying mechanisms for change
[64].

Owing to the intricate factors that influence the decision to prescribe an antimicrobial, not all strategies will work with all GPs in all regions
[2]. The SIMPle study focuses on behavioural changes that are feasible and self-sustaining, given the available resources. The appropriateness of changes and their feasibility within the GP practice setting were also considered
[65].

Formative (qualitative) research explored the culture of antimicrobial prescribing from both the GP’s and the patient’s perspective. Through a series of interviews with GPs (*n* = 16) and focus groups with patients (*n* = 35), the predictors of a GP’s decision to prescribe an antimicrobial and the patient’s expectation to receive an antimicrobial were explored. The questions were guided by a combination of theoretical frameworks, the transtheoretical model
[66] and the buyer behaviour decision-making model
[67], which together explored six key areas: the stage of change, consequences, trade-offs, other influences, segmentation and competition
[68].

As a result of this formative research process, five core outcomes were achieved:

1. The expectations of the patient relating to the UTI consultation with GPs were characterized.

2. The factors that impact the GPs decision to prescribe an antimicrobial were defined.

3. The key messages central to the design and development of this intervention were specified for both the GP and the patient.

4. The results supported the development of quantitative evaluation components, such as a baseline questionnaire to monitor changes in knowledge, attitudes and awareness for both GP and patient.

5. The behavioural theoretical framework underpinning the design and development of this complex intervention was defined.

The multiple interactive components of this intervention were informed by both the peer-reviewed literature and formative research. In short, the SIMPle study will integrate:

• A professional development programme for the GP, which includes interactive workshops, audit and feedback reports on antimicrobial prescribing and electronic antimicrobial prescribing prompts to improve the quality of prescribing. The quality of prescribing is defined within this study as the prospective prescribing of first-line antimicrobials in accordance with the Guidelines for Antimicrobial Prescribing in Primary Care in Ireland.

• Delayed antimicrobial prescribing for UTIs in one study arm, to decrease the consumption of antimicrobials.

• A supportive framework to inform patients of AMR through multimedia applications within the waiting room of the GP.

• Novel e-health technology, which includes an electronic data extraction system that will remotely collect anonymized data from all consultations with patients diagnosed with a UTI by the GPs and mobile health technology to monitor and record antimicrobial consumption behaviour of patients.

By integrating this intervention into routine care and making all material freely available at the end of the intervention, the SIMPle study strives to be sustainable and self-promoting and, thereby, implemented in primary care in Ireland beyond the intervention period.

### Aim and objectives

#### Aim of the SIMPle study

To design, implement and evaluate the effectiveness of a complex intervention on GP antimicrobial prescribing and adult (18 years of age and over) patients’ antimicrobial consumption when presenting with a suspected UTI.

#### Primary objective

To increase the number of first-line antimicrobial prescriptions, as recommended in the Guidelines for Antimicrobial Prescribing in Primary Care in Ireland (2011), for suspected UTIs in primary care by 10% in adult patients.

#### Secondary objectives

1. To compare the effect of the intervention on the frequency of antimicrobial prescribing and antimicrobial consumption in patients presenting with a UTI.

2. To measure the uptake and impact of delayed antimicrobial prescribing for UTIs and the impact of this treatment approach on UTI GP reconsultation visits.

3. To assess a change in cognitive beliefs (knowledge and attitudes) of GPs related to antimicrobial prescribing.

4. To conduct a cost-effectiveness and process evaluation of the SIMPle intervention.

5. To compare the prescribing rates of the intervention arms with regional UTI antimicrobial prescribing rates.

## Methods and design

### Setting

The cluster for this intervention is the practice, and all GPs within each practice will be invited to participate. The baseline population for recruitment of patients will be formed by all practices in the West of Ireland who submit urine samples to the Galway University Hospitals (GUH) laboratory. The most popular patient management software system was chosen, because the SIMPle study builds on remote data extraction, the provision of audit and feedback reports and computer prompts integrated within the GP’s patient management software system. If successful, the intervention could be integrated within the other patient management software systems, of which there are five. In summary, practice eligibility criteria are such that all practices must have the specified patient management software system and submit urine samples to the GUH laboratory.

### Study design

This study will be undertaken in four phases: Phase 1, baseline data collection; Phase 2, GP intervention; Phase 3, patient intervention and Phase 4, endpoint data collection. The study design is summarized in Figure 
1.

**Figure 1 F1:**
[figure not shown]
Study design.

### Implementation

Computerized remote data extraction is facilitated by the Irish Primary Care Research Network (iPCRN)
[69] and patient data are identified through the appropriate coding of suspected UTI consultations in the patient management software system. To promote and encourage consultation coding, which is currently not routine practice, the intervention will be preceded by a coding workshop at the beginning of Phase 1. All practices will be required to register with the iPCRN during or before the coding workshop. Practices will be monitored for two months after the delivery of the workshop to establish uptake of coding, whilst also facilitating a baseline data collection period (Phase 1). Phase 2 will begin with an interactive workshop (intervention arms A and B), which will introduce the intervention components specific to each arm. Phase 3 will see the roll-out of the patient education in all of the practices. The antimicrobial prescribing within each practice will be monitored for six months during Phases 2 and 3 through audit and feedback reports. Evaluation of the impact of the intervention will be carried out in Phase 4.

### Practice identification and randomization

A list of all practices submitting urine samples to GUH was obtained and practices were contacted by phone to establish what patient management software system they used. Practices using the selected patient management software system were thereby identified. The first 30 practices were invited to participate by an invitation letter, which provided an overview of the study, benefits for participation and the contact details of the research team.

Within 10 days of receipt of this invitation, practices were telephoned to determine their interest and willingness to participate in the study. If a practice declined to participate, the reason for not agreeing was recorded and that practice was replaced by another from the eligibility list. This process continued until 30 practices were enrolled. Practices were then randomized to intervention and control arms, using a list of computer-generated numbers. The workshop facilitators were blinded to the allocation throughout the delivery of the coding workshops in Phase 1.

#### Patient eligibility

All patients are eligible if aged 18 years and over and presenting with symptoms of an UTI, as determined by the GP through the consultation coding.

### Patient enrolment

All patients consulting in the participating practices will be informed of the study through information posters in the waiting area from Phase 1.

In Phase 2, GPs will be encouraged to submit a urine sample from each patient presenting with a suspected UTI to the GUH laboratory and request the patient’s mobile telephone number during the consultation. The patient’s mobile telephone number will be recorded on the laboratory diagnostic request form submitted with the urine sample to the GUH laboratory. Mobile telephone numbers will be collected on a daily basis from this laboratory. Each mobile telephone number will be entered into a computer program, which will generate automated text messages. The first text message will confirm consent.

### Sample size

#### Primary outcome: adherence to the guidelines for antimicrobial prescribing in primary care in Ireland (control - intervention arm a)

Previous research has established that 56% of UTI patients receive an antimicrobial, with only 38% of prescriptions made out for the recommended first-line treatment
[8]. Sample size calculations are based on an absolute 10% increase in first-line prescriptions according to guidelines (primary outcome).

Additional assumptions for sample size calculations are:

• Power of 80% and *α* of 5%.

• Practice attrition is dependent on the completeness of consultation coding, which will be monitored and corrected during Phase 1.

• Patient attrition will be close to 0%, as all coded consultations will be included.

• Improvement in the control group due to participation in the coding workshops has been anticipated.

• An intracluster correlation (ICC) of 1% was obtained from a previous study in this area
[6,12].

A total sample size of 920 patients recruited from 20 practices gives a power of 80% to detect a significant change in the proportion of patients to receive first-line antimicrobial when treated for UTI when the ICC is 1%.

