### GP components

#### Intervention workshops

A coding workshop will be delivered to all practices at the beginning of Phase 1. Routine coding for UTIs using the International Classification of Primary Care code (U71: 'cystitis, urinary infection, other’) will be demonstrated. The advantage of routine coding of UTI consultations will be to facilitate the generation of electronic audit and feedback reports, which will be extracted through the iPCRN system (see further).

Contact information for GPs (for example, mobile telephone numbers, email addresses) will also be collected to facilitate reminders to code throughout the study period.

Phase 2 will begin with an interactive workshop for intervention arms A and B. The interactive workshops promote changes (where necessary) in antimicrobial prescribing for the treatment of UTIs by presenting an overview of prescribing and AMR, discussing the role of the GP in the spread of AMR and the potential positive impact of prescribing according to guidelines.

In addition, the interactive workshop delivered to practices in intervention arm B will support the GPs in recommending delaying antimicrobial treatment by 48 hours where appropriate. Based on the information provided in the workshop, the GP can discuss the benefits of delayed antimicrobial treatment for UTIs with the patient. This two-way communication will encourage patients to make an informed decision on their treatment. The decision to delay treatment will be shared between the GP and the patient.

The workshops will be delivered to each practice by members of the research team. General practitioners attending the workshops can receive continued professional development recognition for their participation from the Irish College of General Practitioners.

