#### Computer prompt application

For intervention arms A and B, a computer prompt has been developed for use within the selected GP practice management software system. This prompt summarizes the recommendations for first-line antimicrobial treatment and will appear on the computer screen when the GP enters the International Classification of Primary Care code (U71) for 'cystitis, urinary infection, other’. In addition, for practices in intervention arm B, the prompt will include a recommendation to consider delayed antimicrobial prescribing. In intervention arms A and B this prompt will also remind the GP to collect patients’ mobile telephone numbers.

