#### Consultation data

For the purpose of the intervention, UTI consultation data will be extracted remotely through the iPCRN. Extracted anonymized consultation information will be comprehensive and will include, at a practice level:

• Total number of consultations per month;

• Total number of consultations for UTIs per month (coded U71);

• Practice information (GPs, practice nurse, dispensary);

• Number of times an audit was generated (to monitor coding).

For the patients, the following information will be collected:

• Consultations (numbers, dates);

• UTI consultations (dates);

• Urine sample results (date, outcome, resistance profile);

• Antimicrobial prescribing (type, date, dosage);

• Other prescribed medication (type, date, dosage);

• Demographic data including age, sex, medical card status and comorbidities (if coded).

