### Limitations of the study

The method of data collection used requires a coding workshop to improve routine consultation coding for UTIs in all practices participating in the intervention, including those in the control group. The inclusion of the control group in the coding workshop may affect the outcome; however antimicrobial treatment was not discussed at these workshops. To limit this bias, researchers delivering the workshops were blinded as to randomization of practices to intervention and control. This bias is anticipated to increase awareness in the control group, resulting in a potentially smaller difference between intervention and control arms.

Computerized remote data extraction will be used to assess differences between the intervention and control arms. Data analysis will not be blinded. However, as the outcome is an absolute comparison in first-line prescriptions of antibiotics, before and after the intervention, the risk of bias is minimal.

The use of patient mobile telephone numbers for evaluation purposes, while novel and direct, introduces selection bias, owing to different levels of mobile phone penetration and familiarization with their use. For research evaluation purposes, however, the implementation of follow-up by mobile telephone technology allows evaluation of consumption (and thereby the impact of delayed prescribing) rather than simply the evaluation of prescribing behaviour by GPs. However, since the sample can be related back to the source population and the selection bias can be estimated, the final evaluation can be considered within this context.

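### Entry to the primary analysis depends on U71 coding by unblinded GPs, which has different consequences by arm in Phases 2-3; the judgement that bias is minimal does not consider this

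*Protocol article*

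**What the plan says.** All references are to the protocol article.

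- **Who is counted.** Under Patient eligibility, adults are eligible if they present with UTI symptoms, "as determined by the GP through the consultation coding". The primary outcome is first-line prescriptions as a percentage of all antimicrobial prescriptions for UTI, and these consultations are found through the code. Practices were randomised before the coding workshops (Practice identification and randomization). Only the workshop facilitators are described as blinded.
- **How settled coding is.** The Implementation section opens its account of the workshop with "To promote and encourage consultation coding, which is currently not routine practice". The Sample size section says completeness of coding is monitored and corrected in Phase 1. It then assumes: "Patient attrition will be close to 0%, as all coded consultations will be included".
- **What all arms share.** "A coding workshop will be delivered to all practices at the beginning of Phase 1". GP contact details are collected "to facilitate reminders to code throughout the study period", with no arm restriction.
- **What only A and B have in Phases 2 and 3.** Entering U71 brings up the prompt on first-line treatment (Computer prompt application; Table 1). "In intervention arms A and B this prompt will also remind the GP to collect" mobile numbers, and Table 1 adds urine samples. Audit reports comparing the practice with the other practices start with Phase 2 in A and B. Control receives its reports at the end of Phase 3. The Consultation data section lists "Number of times an audit was generated (to monitor coding" among the practice-level items.
- **What is said about bias.** Limitations of the study covers raised awareness in control, unblinded analysis ("Data analysis will not be blinded") and selection into text-message follow-up. It judges the risk for the first-line outcome to be minimal because the comparison is an absolute before-after one.

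**The concern.** The GP who chooses the drug also decides, by entering the code, whether that choice is counted. In arms A and B the code has consequences during the outcome period: it shows the GP the recommended drug and adds the prescription to a report comparing the practice with its peers. In control it does neither. If coding then depends on the drug chosen, and does so differently by arm, the first-line share among coded prescriptions is no longer a randomised comparison. A difference could be created or hidden. Complete extraction of coded records would not reveal it, because the missing records are the uncoded ones.

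Entry to the consumption set also depends on GP actions: a urine sample, a phone number on the request form, then the patient's consent by text. The electronic reminder for the first two runs in A and B only.

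**Working it through.** **1. The passages together.** Selection follows randomisation (Practice identification and randomization; Patient eligibility). Correction of incomplete coding is stated for Phase 1 only (Sample size), before the arms diverge. The prompt and the reports then run in A and B only (Computer prompt application; Electronic audit and feedback reports; The control arm). The multilevel model adjusts for baseline prescribing (Method of quantitative data analysis). That cannot remove selection that starts in Phase 2, because the selection changes which later prescriptions are seen.

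**2. The plan's own figures.** The plan gives no coding rate by arm, so there is none to reproduce. The figures used below are the 38% first-line share, the 10-point target, and 920 patients from 20 practices with an ICC of 1%. Read as 10 practices per arm, that is 460 patients per arm, 46 per practice, and a design effect of 1 + 45 × 0.01 = 1.45. Whether 920 itself reproduces depends on sidedness and the split per arm, which the article does not state. This point does not rest on it.

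**3. Illustration: no true effect, selective coding in arm A, unselective coding in control.** Let u be the assumed fraction of non-first-line prescriptions that arm A leaves uncoded. The observed share is 0.38 / (0.38 + 0.62 × (1 − u)).

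- u = 10%: 0.38 / (0.38 + 0.558) = 0.38 / 0.938 = 40.5%, a spurious +2.5 points.
- u = 20%: 0.38 / (0.38 + 0.496) = 0.38 / 0.876 = 43.4%, a spurious +5.4 points.

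The whole 10-point target would need first-line prescriptions to be coded about 1.51 times as often as others: (0.48 / 0.52) / (0.38 / 0.62) = 0.923 / 0.613 = 1.51.

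**4. Effect on the test.** The effective number per arm is 460 / 1.45 = 317. By normal approximation with a two-sided 5% test, the chance of a falsely significant result favouring A is about 9% at u = 10% and 28% at u = 20%, against a nominal 2.5% in that direction. Loss among coded consultations is 0% in every case.

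**5. Direction.** If arm A instead left 10-20% of its first-line prescriptions uncoded, 38% would read as 0.342 / 0.962 = 35.6% to 0.304 / 0.924 = 32.9%. Selective coding in control would move the contrast the other way from the same selection in A.

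**6. Consumption.** The sample size section plans control versus B. The section on frequency of prescribing and consumption compares A with B by text-message response. Both A and B have the reminder, so the imbalance in step 1 bears on the first comparison and largely drops out of the second.

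**The case against.** Much of the case on the other side stands.

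- A reader might infer that the near-zero attrition line is offered as protection against bias. It is not: it is a sample-size assumption. The statement open to challenge is the one in Limitations of the study.
- A reader might infer that the prompt directly increases coding. It appears only after U71 has been entered, so its effect on coding is indirect. The audit reports are the more plausible channel, and even there the link is inferred. Reports are available to download, and nothing in the article says GPs withhold codes according to the drug chosen.
- Control is not left without support. It has the workshop, apparently the coding reminders, and the request for samples and phone numbers throughout the intervention.
- Selection into text-message follow-up is already conceded in Limitations of the study, and the plan compares text participants with non-participants. What is not considered is a difference in capture between arms.
- The monthly totals of all consultations and of U71 consultations are to be extracted, and data are to be compared between arms. The inputs for a coding rate are therefore already planned.
- The unblinded-analysis sentence concerns analysts, not the GPs who code.

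What does not fall away is that inclusion is decided after randomisation, by GPs in different conditions by arm, and that the bias statement for the primary outcome does not address it. An analysis plan may add sensitivity sets, but the article's stated judgement is wrong as it stands.

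**Conclusion.** The concern holds as a risk that the protocol has not considered, not as a demonstrated bias. The judgement that the risk is minimal for the primary outcome is unsupported, because differential coding by arm in Phases 2 and 3 is not discussed and baseline adjustment does not remove it.

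Size and direction are unknown. The range of 40.5-43.4% against a true 38% rests on an assumed 10-20% of non-first-line prescriptions left uncoded in arm A and on unselective coding in control. The documents do not support reading it as an estimate, or inferring that the result must favour arm A.

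For consumption, the imbalance in reminders matters for control versus B and little for A versus B. The two sections that name these comparisons must be reconciled. A broader claim that the consumption analysis is compromised whichever comparison is used would go too far.

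**What to change.** 1. Give control practices the same U71 pop-up with the data-collection reminder only (urine sample, phone number) and no treatment text. Cost: a stripped version of existing software and a small departure from usual care, limited to steps control is already asked to take. It equalises the reminder, not the audit reports.
2. Continue monitoring coding through Phases 2 and 3. Report U71 consultations per 1,000 total consultations, phone-number capture and text consent by arm and phase beside the primary result. Cost: the consultation counts are already extracted; capture and consent need a tabulation.
3. Add a sensitivity analysis of first-line share in a set not defined by U71, for example adults with a urine sample sent to the laboratory, classified by prescriptions around that date. State that urine sampling is itself prompted only in A and B unless item 1 is adopted, so this set is a check and not a replacement. Cost: a wider extraction query, which must fall within the consent given by practices.
4. In Limitations of the study, replace the judgement of minimal risk with a statement that coding may differ by arm, with unknown size and direction.
5. Reconcile the consumption comparison between the sample size section and the analysis section.
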